### NIBS- transcranial direct current stimulation

Transcranial direct current stimulation (tDCS) is currently being investigated as a neuromodulation intervention [14] tDCS has shown beneficial motor behavioral effects in adults [15] and is more cost effective and more portable than another form of NIBS using electromagnetic current called repetitive Transcranial Magnetic Stimulation(rTMS). The mechanism of tDCS involves changing the spontaneous neuronal firing rate and therefore the resting membrane threshold, influencing polarization. Dependent upon the electrode montage and dosing parameters, tDCS involves down-regulating or inhibiting the excitability of the motor cortex in the contralesional hemisphere in an effort to upregulate or disinhibit the ipsilesional hemisphere. Applying *cathodal* tDCS to the contralesional hemisphere has been shown to provide this inhibitory component in adults with stroke, while *anodal* stimulation is excitatory, leading to improved motor function. Importantly, children with diagnoses such as Rasmussen’s Encephalitis, and Schizophrenia have tolerated the use of tDCS well with few minor adverse events such as the sensation of tingling and no reports of pain [16, 17] tDCS has recently been investigated in children with CP and more specifically in our lab in children with unilateral spastic CP with only minor adverse events found [18, 19]. No serious adverse events, such as seizure, have occurred with its use in child or adult populations [14, 20]. Adverse effects of tDCS have been minimized by maintaining current intensity under 2.0 mA and current duration under 20 min. A number of studies have shown that the weak electrical currents applied across the scalp in tDCS are not sufficient to cause tissue damage in the cortex [ 21-23].

### Modes of brain stimulation

As a point of clarity, tDCS should be distinguished from other forms of brain stimulation. For example, traditional electroconvulsive therapy (ECT) induces convulsive activity by delivery of large electrical currents for the treatment of medically refractory depression. In contrast, tDCS influences cortical neurons through the process of neuromodulation, not by the induction of action potentials. Thus, tDCS does not involve the major risks associated with ECT, affecting memory and consciousness. As compared to other non-invasive brain stimulation techniques such as rTMS which carries a low risk of seizure, there have been no reported cases of tDCS inducing seizures either in healthy pediatric or adult human subjects or in child and adult subjects with various neurologic diagnoses[20, 22, 24].

### Change in practice

The significance of this proposed study is that combined CIMT and tDCS could translate research into unprecedented clinical gains in motoric function for individuals with pediatric hemiparesis as 1) the brain during developmental years has a high capacity for plasticity, possibly higher than in adults, 2) neuroplastic change can occur in the injured brain, 3) we are applying a novel neuromodulatory intervention specifically targeted for brain reorganization, and 4) we are combining this intervention with a current clinical behavioral approach (CIMT) that has been shown to influence neuronal excitability and make meaningful clinically important differences.. This could potentially lead to a transformation of rehabilitation practice for this condition Furthermore, even if only a small percentage of the lifetime costs associated with rehabilitating children with hemiparesis were reduced, the aggregate savings would be significant.

Our protocol proposes to non-invasively apply an electrophysiologic intervention with the clinically mature therapy of CIMT. Changes in functional brain connectivity after CIMT have been found in adults and children[10, 25, 26]. However, little research has been performed using non-invasive brain stimulation in pediatric rehabilitation and even less with combined interventions. This project combines a unique form of noninvasive brain stimulation (tDCS) with a behavioral treatment (CIMT) to promote a combined intervention that could achieve higher recovery in pediatric hemiparesis than current treatment alone provides. Both modalities impact excitability of the brain, yet this synergistic approach is novel in children with hemiparesis. The protocol includes measurement of functional and morphologic changes in the brain with neuroimaging and TMS testing to show “proof of principle” data, enriching our understanding of connectivity and responders to intervention. The expected outcomes are no serious adverse effects, improved hand function, and improved functional connectivity of the affected hemisphere.

## Methods/design

### Ethical considerations

This study has been approved by the University of Minnesota and Gillette Children’s Specialty Healthcare Institutional Review Boards. Approval by the University of Minnesota Clinical and Translational Science Institute (UMN CTSI) and its Scientific Review Committee, as well as Center for Magnetic Resonance Research (CMRR), was also obtained. All caregivers and children will be given oral and written information about the study before a request for formal informed consent/assent is signed.

### Objectives

The primary objective of the proposed project is to determine the feasibility of the study design as well as to assess the synergistic effect of combined tDCS/CIMT on safely improving hand motor function in children and young adults between the ages of 8 and 21 with hemiparesis.

### Hypotheses

Children with hemiparesis randomized to intervention (tDCS/CIMT) or control (sham tDCS/CIMT) will not display any seizure activity or other serious adverse effect.The intervention group will show greater improvement in paretic hand function (force production, speed, quality of movement) than will controls.The intervention group will show greater improvements in self-reported levels of participation and satisfaction with rehabilitation goals as evidenced by the COPM.

The secondary objective is to examine the influence of combined tDCS/CIMT on brain excitability and reorganization.

### Hypotheses

Children in the tDCS/CIMT group will show significantly greater excitability in the ipsilesional hemisphere than will controls.Changes in brain excitability and reorganization will correlate with positive changes in motor function.

### Study design

The study will use a randomized, sham-controlled, pretest-posttest-follow up design involving two groups of 10 children with hemiparesis and unilateral infarct or periventricular leukomalacia as confirmed by MRI (total sample size = 20). (Fig. 1). This protocol is registered on clinicaltrials.gov (# NCT02250092)

**Fig. 1 Fig1:**
[figure not shown]
Flowchart of tDCS/CIMT study adapted from the Consolidated Standards of Reporting Trials (CONSORT). AHA: Assisting Hand Assessment, CIMT: Constraint-Induced Movement Therapy, COPM: Canadian Occupational Performance Measure, DTI: Diffusion Tensor Imaging, MRI: Magnetic Resonance Imaging, rs-fMRI: resting-state functional Magnetic Resonance Imaging, tDCS: transcranial Direct Current Stimulation, TMS: Transcranial Magnetic Stimulation

### Recruitment

We will use our established database of over 200 families to begin recruitment of children with hemiparesis, plus talks at local pediatric facilities, mailings, posting on related websites and newsletters. Incorporation of CIMT provides a motor training component to the study, and families are more willing to participate with the promise of receiving what would be an otherwise expensive intervention now covered by the study.

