### Inclusion criteria

Subjects will be eligible to participate in the study if the following conditions exist:Hemispheric Stroke or Periventricular Leukomalacia confirmed by most recent MRI or CT radiologic report with resultant congenital hemiparesis≥ 10 degrees of active motion at the metacarpophalangeal jointNo evidence of seizure activity within the last 2 yearsPresence of a motor evoked potential from at least the contralesional hemisphere if not both hemispheresAges 8–21 yearsIf ages 8–17, able to give informed assent along with the informed consent of the legal guardianChildren who have had surgeries, which may influence motor function e.g.- tendon transfer, will be included, yet surgical history will be documented

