### Prior and concomitant therapy

Behavioral therapies including occupational, physical or speech therapies will be allowed both during both the intervention and follow-up period. These therapies will be documented and reported.

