### Blinding

The investigator who performs the testing, the CIMT interventionists and the physician who does the evaluations will be blinded to the treatment arm as will the child/caregiver/family. The study biostatistician, study coordinator and principal investigator (PI) will be unblinded. The following procedure will be employed:The study biostatistician will provide sealed envelopes to the study coordinator.The study coordinator will share the group assignment with the principal investigator in a secure private room, in the absence of the physician, research tester, subject legal guardian and subject. The Medical Monitor to the study will have access to the group assignment.Blinding is applied through designated settings on the tDCS machine of sham or real tDCS. The unblinded investigator who administers the tDCS (PI: [name]) will, during the intervention, switch the setting on the tDCS device to the designated placebo setting, hidden from view of the subject. For the first 30-seconds of either setting, a gradual “ramp-up” sensation of the stimulation occurs. This is built into the machine for both settings. However, for the sham stimulation, the sensation then abates, and not until the end of the 20-minute session does the subject receiving the 30-seconds of “ramp-down” sham once again experience the sensation. The sensation then occurs and “ramps-down” the amperage until the machine turns off.Information on subject group assignment will be logged and stored in a designated locked cabinet at the study coordinators office.

Outcome Assessments. We incorporated the body function/structure and activity/participation domains of the International Classification of Functioning, Disability and Health [2727].

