##### Rationale for use of tDCS

Our previous research incorporated rTMS, which although promising as an intervention, has limitations especially with children [36, 37]. Our recent results demonstrate not only safety and but also reveal significant improvements in hand function with rTMS combined with constraint-induced movement therapy, yet we foresee the possible greater benefits from using tDCS over this type of non-invasive brain stimulation in pediatric hemiparesis. (REF) First, both of the interventions, tDCS and CIMT, applications of tDCS/CIMT can occur concurrently whereas it is difficult to incorporate the use of rTMS *at the same time* as performing behavioral therapy with the affected upper extremity. Applying tDCS/CIMT simultaneously could optimize neuroplastic principles of concurrent firing of neurons and strengthening of neuronal networks [38, 39]. Second, tDCS may reduce costs. As rTMS can be ten times the current cost of tDCS, cost may become prohibitive when considering rTMS. Additionally, if the application of tDCS reduces the need for additional therapies, a further costs savings could be realized. Third, use of rTMS has resulted in reports, albeit rare, of adverse events such as seizures and syncopal episodes, in both adults and children [40, 41] .

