## Discussion

We outline the background and design of a trial with two intervention groups comparing the effects of tDCS on children and young adults with hemiparesis receiving CIMT. The design of this study is predicated upon positive outcomes previously established with CIMT. Additionally, we incorporate consideration of trials we have completed with neuromodulation interventions of repetitive transcranial magnetic stimulation and a tDCS pilot with this population [19, 36, 48]. The proposed study design pursues investigation of a synergistic effect achieved by combining rehabilitation (CIMT) and neuromodulatory (tDCS) interventions. The study hypotheses reflect the importance of safety, feasibility and efficacy surrounding this dual intervention. As non-invasive brain stimulation in pediatric hemiparesis is in a nascent investigational phase, understanding the potential value of such interventions is paramount.

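### The eligibility list does not exclude children who have already received active tDCS, although recruitment starts from a group that has run a tDCS pilot in this population, so blinding of child and family can fail

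*Protocol article*

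**What the plan says.** Recruitment section: "We will use our established database of over 200 families to begin recruitment of children with hemiparesis". Other routes, such as outreach to local clinics and online notices, are listed as additions.

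The group's earlier work appears in three places. The background section on tDCS says that the method has been studied "more specifically in our lab in children with unilateral spastic CP with only minor adverse events found". The rationale section reports "significant improvements in hand function with rTMS combined with constraint-induced movement therapy". The Discussion refers to "trials we have completed with neuromodulation interventions of repetitive transcranial magnetic stimulation and a tDCS pilot with this population".

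The eligibility lists say nothing on earlier stimulation, earlier trial participation or earlier CIMT. Their only time-limited treatment exclusion is six months for botulinum toxin or phenol. Children with earlier surgery "will be included, yet surgical history will be documented". The section headed Prior and concomitant therapy covers only therapy after entry: "Behavioral therapies including occupational, physical or speech therapies will be allowed both during both the intervention and follow-up period".

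The Blinding section requires child, caregiver and family to be blinded. It describes the sham as follows: "for the sham stimulation, the sensation then abates, and not until the end of the 20-minute session" does the child feel it again.

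**The concern.** A sham of this kind works on a child who does not know what a full active session feels like. A child who has had one, and a caregiver who remembers the child's account of it, can notice that the sensation has gone after the first minute or so. Nothing in the eligibility lists keeps such a child out, and recruitment begins with the families most likely to include one.

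The outcomes at stake are those that the family reports. The COPM is self-rated and has its own hypothesis under the primary objective. Symptom reports and the tolerance survey are completed by subjects and caregivers, and the abstract counts symptom reports within its primary safety outcome. Blinding lost in this way cannot be restored at analysis.

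**Working it through.** The point turns mainly on setting sections of the protocol article side by side.

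1. **Can a former tDCS participant be approached?** Yes. Recruitment starts from the group's own database, and the group has run a tDCS pilot in the same population. That the database holds pilot families is an inference. The article does not say so.

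2. **Did the earlier work deliver current to children?** The intervention section calls the earlier pilot (reference 19) a computerized modeling pilot, which could suggest that no child was stimulated. The background section cites references 18 and 19 for tDCS in children with CP, including the group's own laboratory, and reports adverse events. So at least some children were stimulated. The number of children and sessions is not given.

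3. **Would such a child be excluded?** No. None of the listed inclusion or exclusion criteria concerns previous stimulation.

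4. **What could the child compare?** The ramp-up in sham lasts 30 seconds according to the Blinding section, and 30 seconds to 1 minute according to the control-group section. The ramp-down lasts 30 seconds. Over a 20-minute session the sham sensation is therefore present for about:
   - (0.5 + 0.5) / 20 = 5% of the time, up to
   - (1.0 + 0.5) / 20 = 7.5% of the time.

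   The Blinding section presents the fading as the feature that sets sham apart from real stimulation, so it implies that the real sensation continues. It does not say for how long or how strongly.

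5. **Which outcomes are exposed?** COPM, symptom reports and the tolerance survey come from the child or family. The AHA uses a standardized video-recorded session, and the tester, the CIMT interventionists and the physician are blinded.

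6. **How large is the effect?** One child is 1/20 = 5% of the sample and 1/10 = 10% of an arm. The number of former participants is not given, so this cannot be carried through to an outcome.

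As a yardstick for the AHA, the plan's own power figure reproduces. With SD 7.1, correlation 0.8 and 10 per group:
- V = 2 × 7.1² × (1 − 0.8²) = 36.3
- standard error of the difference = √(36.3 / 10) = 1.905
- power for 5.4 points = Φ(5.4 / 1.905 − 1.960) = Φ(0.874) = 80.9%, against the stated 80%.

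The proposed change affects eligibility only and leaves this calculation as it is.

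**The case against.** The strongest reply has four parts.

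**The overlap is inferred, and an article condenses a fuller protocol.** The first half stands: no count of former participants is given. The second half carries less weight. The article sets out its criteria as lists and includes a washout for one earlier treatment, so what it does state admits these children.

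**The AHA is protected.** This largely stands. A child's guess does not unblind the tester. An effect through effort in the home program is possible, but nothing in the document shows it.

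**rTMS is a different technique.** This stands. A former rTMS participant has no reference for the feel of tDCS, so a reader should not infer that every former trial participant can tell real from sham.

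**Recent CIMT or rTMS/CIMT does not bias the comparison.** A reader might infer that carry-over from earlier training distorts the AHA result and that a CIMT washout is therefore required. The document does not support that. It describes the rTMS work as completed and gives no dates, so recent exposure is speculation. Suppose, with no source, that a previously trained child gained 5 points less, which is nearly the whole 5.4 points assumed for treatment. One net child of imbalance would then shift an arm mean by 5/10 = 0.5 points. That is 0.5/1.905 = 0.26 of a standard error and 0.5/5.4 = 9% of the difference the trial is powered for. Under randomization such an imbalance is chance variation, not bias, and any lasting effect on AHA level is in the baseline that ANCOVA adjusts for. A change in remaining response would not be adjusted for, which is a reason to record the exposure.

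**Conclusion.** The point holds in a narrow form: as written, the criteria admit children who have already received active tDCS to a trial whose participant blinding depends on their not recognizing a sham that fades. It bears mainly on the COPM and on the symptom and tolerance reports, and less on the AHA.

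Its size cannot be stated beyond 5% of the sample per such child. It rests on two assumptions: that some pilot families are in the database or come through another route, and that a child can recognize the difference in sensation. The article makes both plausible and proves neither.

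The material does not support a blanket exclusion of former rTMS participants, a particular CIMT washout period, or any stated loss of power. This is a worthwhile, inexpensive improvement and not a flaw that undermines the primary comparison.

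**What to change.** Add previous active tDCS, including the group's own pilot, to the exclusion criteria. State that earlier single-pulse TMS testing does not exclude a child.

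Record prior rTMS and recent CIMT at screening, with dates, and report both by arm. Add a sensitivity analysis, for example repeating the between-group comparison without the children so exposed. With 10 per arm it would be descriptive. Whether to set a CIMT washout, and how long, is for the investigators to decide.

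The exclusion has to be in place before enrolment. The cost is a short amendment and a few screening questions. The pool becomes slightly smaller, in a population that the Study protocol section already describes as greatly limited by the motor evoked potential requirement. Against that stand a database of over 200 families and the other recruitment routes.

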### Participants- inclusion and exclusion criteria

Children and young adults, ages 8–21, with hemiparesis due to perinatal stroke or periventricular leukomalacia will be recruited for the study based on the following eligibility criteria:

### Inclusion criteria

Subjects will be eligible to participate in the study if the following conditions exist:Hemispheric Stroke or Periventricular Leukomalacia confirmed by most recent MRI or CT radiologic report with resultant congenital hemiparesis≥ 10 degrees of active motion at the metacarpophalangeal jointNo evidence of seizure activity within the last 2 yearsPresence of a motor evoked potential from at least the contralesional hemisphere if not both hemispheresAges 8–21 yearsIf ages 8–17, able to give informed assent along with the informed consent of the legal guardianChildren who have had surgeries, which may influence motor function e.g.- tendon transfer, will be included, yet surgical history will be documented

### Exclusion criteria

Subjects will be excluded from participation in the study if any of the following conditions exist:Metabolic DisordersNeoplasmEpilepsyDisorders of Cellular Migration and ProliferationAcquired Traumatic Brain InjuryPregnancyIndwelling metal or incompatible medical devicesEvidence of skin disease or skin abnormalitiesBotulinum toxin or Phenol block within the last six-months

### Prior and concomitant therapy

Behavioral therapies including occupational, physical or speech therapies will be allowed both during both the intervention and follow-up period. These therapies will be documented and reported.

### Exit criteria

Subjects will exit the study if any of the following conditions exist:Subject voluntarily withdraws from the study.Subject acquires any of the listed exclusion criteria.Subject completes the protocol.Subject’s well-being, in the opinion of the Investigator, would be compromised by study continuation.Subject experiences a serious adverse event or seizure.Medical monitor and/or IRB recommendation

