**Methods/design:**

A randomized, controlled, double-blinded clinical trial. Twenty children and/or young adults (ages 8–21) with congenital hemiparesis, will be enrolled. The intervention group will receive ten 2-hour sessions of transcranial direct current stimulation combined with constraint-induced movement therapy and the control group will receive sham stimulation with CIMT. The primary outcome measure is safety assessment of transcranial direct current stimulation by physician evaluation, vital sign monitoring and symptom reports. Additionally, hand function will be evaluated using the Assisting Hand Assessment, grip strength and assessment of goals using the Canadian Occupational Performance Measure. Neuroimaging will confirm diagnoses, corticospinal tract integrity and cortical activation. Motor cortical excitability will also be examined using transcranial magnetic stimulation techniques.

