### Primary outcome measure

The Assisting Hand Assessment (AHA) scaled score will be used as the primary outcome measure as a test of unilateral limb dysfunction; it is based on a child’s usual performance in relevant activities. This test uses a standardized video-recorded play session. Activity is assessed on 22 items using a 4-point rating scale. The range of raw scores is 22–88 points, with higher scores indicating better ability. Excellent interrater (0.97) and intrarater (0.99) reliability has been found using this tool and it has been found to have high validity in use with children[28-30]

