In addition to its economy and portability, tDCS has shown improvements in motor function in adults with and without the concurrent use of CIMT [42, 43]. The rationale for the investigation of tDCS in the pediatric population is that the use of non-invasive brain stimulation could translate more efficiently into clinical applications thus improving the quality of life for children with hemiparesis. And tDCS safety, when using standard guidelines, is supported in the literature as to having common side effects limited to mild and reversible skin irritation. Specific to the tDCS model we are using (Soterix LTE 1×1 tDCS, NY, NY), the design reduces skin irritation by conditioning the skin prior to stimulation and allowing the device operator to incorporate subject feedback and adjust the controls without stopping. This model was specifically chosen for our project because of its adaptability to resistance changes between the surface electrodes and the subject. The model uses two 9 V batteries to administer stimulation. As a safety feature, the unit will automatically reduce the applied voltage so as to maintain a low voltage level. The built-in ramp-up and ramp-down features allow for gradual administration of the current. Another component of this device specifically designed for children is the adjustable strap that allows for optimal contact of the surface electrodes with the skin for reduced irritation.

Safety. Safety testing includes a physician screening with a modified pediatric stroke outcome measure at pretest, interim day 5, posttest and follow-up sessions. Additionally, vital signs are assessed before and after each tDCS/CIMT session and subjects and caregivers complete a subject report of symptoms and a tolerance survey.

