##### tDCS/CIMT control group

Children in this group will receive the same procedures and home program as the intervention tDCS/CIMT group but, the tDCS device will be set to a specific placebo setting which extinguishes the current after a 30 s to 1 min ramp-up phase and gradually reintroduces the ramp-down at the end of the 20 min session. This feature allows for placebo control and blinding.

Statistical Analysis. There are 3 analysis populations planned. Intent-to-treat (ITT) will include any subject randomized according to their treatment assignment. Per-protocol (PP) will include randomized subjects without major protocol violations and who were compliant (at least 80 % of planned sessions with their treatment assignment. A detailed list of the major protocol violations warranting exclusion from the PP analysis will be determined prior to trial commencement. The Safety population will include all subjects who receive treatment, according to treatment received. We do not anticipate these groups to differ. The safety profile will use the safety population and be primarily descriptive in nature reporting the number and percentage of adverse events for the two treatment groups and include an aggregate breakdown by severity, seriousness, and frequency (within a patient). Within-group analysis of continuous outcomes comparing posttest to pretest will be done with paired t-tests. Between-group analysis of continuous outcomes comparing the mean change from pretest to posttest between treatment groups will be adjusted for baseline values in the fashion of ANCOVA for added precision. The primary analysis will be based on the ITT population with complementary analyses using the PP population. The association between changes in brain excitability/reorganization and motor function will also be evaluated and based on linear regression. P-values less than 0.05 will be considered statistically significant.

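### The exit rule ends study participation, not only stimulation, after a serious adverse event, a seizure or a new exclusion criterion, so posttest and safety data can be lost for reasons tied to outcome

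*Protocol article*

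**What the plan says.** The Exit criteria section of the protocol article opens with "Subjects will exit the study if any of the following conditions exist". The list that follows includes "Subject experiences a serious adverse event or seizure" and "Subject acquires any of the listed exclusion criteria". These stand beside voluntary withdrawal, completion of the protocol, the investigator's opinion on the child's well-being, and a recommendation of the medical monitor or IRB. Nothing in the article provides for assessment after exit.

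Three other parts of the article rely on data collected after such an event:

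- **Safety schedule** (Safety paragraph under Rationale for use of tDCS): "physician screening with a modified pediatric stroke outcome measure at pretest, interim day 5, posttest and follow-up sessions".
- **Analysis** (Statistical Analysis paragraph): "Intent-to-treat (ITT) will include any subject randomized according to their treatment assignment". The primary analysis uses this population, and the between-group contrast is the change from pretest to posttest, adjusted for baseline. Adverse events are to be broken down by severity, seriousness and how often they occur within a patient.
- **Primary outcome**: the abstract states "The primary outcome measure is safety assessment of transcranial direct current stimulation by physician evaluation", while the Primary outcome measure section states "The Assisting Hand Assessment (AHA) scaled score will be used as the primary outcome measure". The exit rule bears on both.

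**The concern.** The rule as written ends participation in the study, and two of its triggers are the events that the first hypothesis is about: seizure and other serious adverse effects. A child who has such an event before posttest stays in the ITT set without the outcome that the set is meant to compare. The same child also misses the later physician screens, which would show whether the event resolved or recurred.

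Data lost in this way are not missing at random with respect to harm. The loss could also be unequal between arms. Evidence of skin disease or abnormality is on the exclusion list, and acquiring a listed criterion triggers exit. The protocol describes stimulation as having "common side effects limited to mild and reversible skin irritation". Active current runs for the 20-minute session, whereas the sham setting extinguishes it after ramp-up. Read literally, a mild and expected effect could therefore remove children, plausibly more of them from the active arm.

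With 10 children per arm, one exit is 10% of an arm.

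**Working it through.** **1. What is lost, by time of exit**

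| Exit | Triggering event | Posttest AHA (primary contrast) | Later physician screens |
|---|---|---|---|
| Before posttest | Counted | Missing | Posttest and follow-up lost, and day 5 if exit is earlier |
| After posttest | Counted | Present | Follow-up lost |

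Only exits during the two-week treatment course, before posttest, affect the primary AHA contrast. Both kinds affect the safety description. If the first serious event ends observation, the within-patient count of serious events is in effect capped at one.

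**2. The plan's own power figure**

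Inputs from Sample size/power: difference 5.4, conservative SD 7.1, correlation 0.8, two-sided alpha 0.05, 10 per group. No allowance for loss is stated there.

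- Adjusted SD = 7.1 × √(1 − 0.8²) = 7.1 × 0.6 = 4.26.
- Standard error = 4.26 × √(1/10 + 1/10) = 1.905.
- Power = Φ(5.4/1.905 − 1.96) = Φ(0.874) = 80.9%.

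The stated 80% is reproduced, but only if all 20 children contribute a posttest value.

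**3. The same formula with exits before posttest**

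| Children with posttest | Standard error | Power |
|---|---|---|
| 10 v 10 | 1.905 | 80.9% |
| 9 v 10 | 1.957 | 78.8% |
| 9 v 9 | 2.008 | 76.7% |
| 8 v 8 | 2.130 | 71.7% |

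A t reference with n₁ + n₂ − 3 degrees of freedom gives 76.2%, 73.6%, 71.0% and 65.0% for the same rows. The level is lower, and the fall for one loss per arm is similar (5.2 points against 4.2).

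**4. How likely an exit is**

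The protocol gives no rate, so this is assumed. With exit probability q per child, the chance of at least one exit among 20 is 1 − (1 − q)²⁰: 33% at q = 2%, 64% at 5%, 88% at 10%. These cover exits at any time, not only before posttest.

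**5. Shift in an arm mean**

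Suppose one of 10 children is lost and that child's change would have been d points below the mean of the other nine. The full-arm mean is d/10 lower than the observed mean.

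- d = 5: shift 0.5 point, which is 0.5/2.4 = 21% of the 2.4-point minimal clinically important difference.
- d = 10: shift 1.0 point, which is 42% of it.

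Both values of d are illustrative. Against the adjusted SD of 4.26 they are 1.2 and 2.3 SDs, so the second is an extreme child.

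**The case against.** The strongest reply is that the exit list is a short entry in a condensed article. It includes completing the protocol, so it may only mark the end of participation. Following an event to resolution, or an exit visit, may be set out in the full protocol, and the handling of missing outcomes in an analysis plan. That stands as far as missing detail goes, and no absent method is counted here. It does not remove the point, because the rule that is stated, followed literally, works against the ITT analysis and the safety visits that are also stated.

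A second reply is that exits should be rare. The article reports no serious adverse event or seizure with this form of stimulation, and entry requires no evidence of seizure activity in the last two years and no epilepsy. This limits the expected number of exits for serious events. It says less about exits for acquired exclusion criteria.

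A reader might also infer more than the documents support:

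- **That the safety outcome is cut off when it occurs.** It is not. The triggering event is recorded, the child stays in the safety population, and the yes/no hypothesis of no serious event remains assessable up to exit.
- **That ITT analysis becomes impossible.** It becomes incomplete for children who exit before posttest. They remain in the set with a missing value.
- **That botulinum toxin or pregnancy during follow-up removes the primary outcome.** By then the posttest AHA has been obtained, and only follow-up data are lost.
- **That the bias favours a known arm or has a known size.** Nothing in the article links serious events to poor AHA change, and no exit rate or deviation is given.

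**Conclusion.** The point holds as a conflict between stated rules. The Exit criteria end study participation for reasons tied to the safety endpoint, while the ITT primary analysis and the scheduled physician screens presuppose continued observation. What may be lost is the posttest AHA of a child who exits before posttest and, for any child who exits, the remaining safety screens and with them the course, recovery and recurrence of the event. The loss is related to outcome. It could differ by arm if skin irritation is treated as an acquired skin abnormality, which is a literal reading and not a stated intention.

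The size cannot be fixed from the documents. On the protocol's formula and conservative inputs, each lost child costs about 2 points of power. This matters less than the informative nature of the loss, since no analysis can recover safety observations that were never made.

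**What to change.** Reconcile the Exit criteria with the Safety and Statistical Analysis paragraphs by splitting the list into two: conditions for discontinuing stimulation, and conditions for ending observation.

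- Leave the criteria for stopping stimulation as they are.
- Keep children who stop in the AHA and physician visits already scheduled, and analyse them in the arm assigned. The exceptions are withdrawal of consent or assent, or a judgement by the investigator, medical monitor or IRB that further assessment would compromise the child.
- Record an acquired exclusion criterion, with its date, as an intercurrent event and not as a reason to end observation.

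The cost is a change of wording and at most one or two already planned visits per discontinued child.
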